**Methods:**

We selected eligible participants using an effective electronic questionnaire containing the inclusion and exclusion criteria and a brief electronic cognitive test. One-third of the respondents with the worst cognitive scores on the electronic test are randomized to group A, starting with a 3-month probiotic intervention, and to group B, starting with a placebo. In a crossover design, both groups change their intervention/placebo status after 3 months for the next 3 months. Participants refusing longer personal assessments due to the COVID-19 pandemic were randomly allocated to one of two subgroups assessed online. Participants in both groups are matched in age, education, gender, and cognitive scores on electronic testing at baseline. At three time points, participants are assessed using a neuropsychological battery, self-report measures of mood, a physical fitness test, blood, urine, and stool samples, and actigraphy. A subset of participants also provided their biological samples and underwent the neuropsychological battery in an extended testing phase 3 months after study termination to find out the long-term effect of the intervention.

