The recruitment of participants is displayed in Figure 1. Hundreds of individuals completed the electronic questionnaire. Of those, 492 fulfilled all the criteria for participation in our study. Choosing only those participants with possible memory impairment using an ALBAV score ≤ 20 resulted in a further reduction of eligible participants to 136. The resulting number of participants represented 28% of the total, with the worst memory performance of the group that filled out the electronic recruitment questionnaire and the electronic memory test ALBAV and fulfilled all the criteria (*n* = 492). A final group of 91 participants was divided into two subgroups. A small subgroup (*n* = 19) of participants feared the COVID-19 infection during the pandemic. Thus, they were assessed with cognitive tests remotely *via* computers using monitors, web cameras, speakers, and microphones. Our experinces with distant testing were described recently (Polanska and Bartos, 2022). The rest of the procedures included completing self-report questionnaires, physical condition tests, and sample collection in person. All procedures were performed in person on the remaining 72 individuals.

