**FIGURE 2 F2:**
[figure not shown]
A cross-over design of the clinical trial with probiotics. T1 denotes the time of first visit when participants were assessed with the PROCOG cognitive battery. The two groups received both probiotic and placebo tablets but in a reverse order. At T2 the participants brought back baseline urine and stool samples and their blood was collected. They also got the first set of probiotic/placebo tablets. All examinations and procedures from T1 and T2 were repeated at T3 when the participants got the second set of probiotic/placebo tablets. All examinations and procedures similar to T3 were repeated at T4 and T5.

All 91 participants were divided into two subgroups based on the order in which they completed the electronic registration form. One subgroup included participants with odd position numbers; the other one had even numbers. After checking for statistically significant sociodemographic differences between two subgroups, a few individuals were exchanged between these subgroups. This ensured that both subgroups matched in age, education, gender, and ALBAV scores before the start of the trial. Unexpectedly, 19 participants did not wish to come for testing in person due to the COVID-19 pandemic. Therefore, they were transferred from in-person to online assessment. These individuals were removed from the original allocation to online subgroups of participants.

A crossover design did not strictly confine one group of individuals to an intervention or placebo. Each group received both placebo and probiotics in tandem for 3 months each, but in reverse order. Members of group A start with a 3-month use of probiotics and continue with a 3-month use of placebo. The order of tablets is reversed for group B. There was no washout period between treatments.

Both participants and administrators were blinded to the type and order of intervention and placebo.

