## Proposed analysis

Data on the cognitive outcomes of the participants will be analyzed separately for groups evaluated in person and online. The results of online participants were exploratory due to the low sample size. Biochemical, self-report, and physical fitness outcomes were collected in person for all participants and were analyzed together. Statistical analyses will be conducted using R or Statistica.

Descriptive statistics will be calculated for primary and secondary outcomes at each visit.

The analysis will proceed using a between-subjects unpaired *t*-test at each time point or using a within-subjects paired *t*-test to compare results between time points.

Additionally, we will include apolipoprotein E allele status and its influence on outcomes.

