### Power calculation

Given our sample size, we will able to detect the effect size of Cohen’s d = 0.43 in the matched-pairs two-tailed *t*-test, assuming power = 0.8 and α = 0.05. This will be d = 0.51 in those tests when only in-person data could be used.

For between-group comparisons, we could detect the effect size of Cohen’s d = 0.59 in a two-sample two-tailed *t*-test, assuming power = 0.8 and α = 0.05. This would be d = 0.67, assuming the use of only in-person data.

All power calculations were performed in G*Power 3.1.9.7 Software (Faul et al., 2007). As we did not attain equal group numbers, the sensitivity of the matched-pairs *t*-test is computed for the smaller group. This means we could detect a slightly smaller effect size for larger groups than reported here.

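### Per-visit between-group tests on all 91 participants ignore the in-person/online subgroups, which the plan's own sensitivities imply are unevenly split (minor)

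*Protocol article*

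**What the plan says.** The Proposed analysis section analyses the cognitive outcomes separately for in-person and online participants. It treats the remaining outcomes differently: "Biochemical, self-report, and physical fitness outcomes were collected in person for all participants and were analyzed together". The test is then fixed: "The analysis will proceed using a between-subjects unpaired" t-test at each time point, or a paired t-test between time points. No term for the in-person/online subgroup is mentioned.

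On how the online subgroup arose, the Participant recruitment and allocation section says "A final group of 91 participants was divided into two subgroups" and "A small subgroup (*n* = 19) of participants feared the COVID-19 infection during the pandemic"; the other 72 did everything in person. The abstract adds: "Participants refusing longer personal assessments due to the COVID-19 pandemic were randomly allocated to one of two subgroups assessed online". The Trial design section says that the 91 were first divided and matched on age, education, gender and ALBAV score, and that the 19 were then moved: "These individuals were removed from the original allocation to online subgroups of participants". It describes no re-matching.

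The Power calculation section gives detectable effects of 0.43 (all participants) and 0.51 (in person only) for the paired test, and 0.59 and 0.67 for the two-sample test. It adds "As we did not attain equal group numbers, the sensitivity of the matched-pairs" t-test is computed for the smaller group.

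**The concern.** The plan keeps the two subgroups apart for cognition and then merges them for self-report, biochemical and fitness outcomes without carrying the subgroup in the comparison. The online subgroup is defined by fear of infection. A link with anxiety and mood scores (BAI, BDI-II, GDS, the anxiety scale) is plausible. For metabolomics or neurofilament it is much less obvious. The matching variables do not cover it.

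This matters only if the online participants are unevenly divided between groups A and B. In that case any outcome difference between online and in-person participants enters the group A minus group B difference at a visit. It would raise the conditional error rate of that test, and would lower or raise its power according to direction.

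**Working it through.** **Inputs.** Total 91, online 19, in person 72 (Participant recruitment and allocation). Detectable d of 0.43 and 0.51 paired, 0.59 and 0.67 two-sample (Power calculation), "in the matched-pairs two-tailed *t*-test, assuming power = 0.8 and α = 0.05"; the same power and α are stated for the two-sample test. The online v in-person outcome difference D, in within-subgroup SDs, is not given. It is **assumed** to be 0.25 to 0.5.

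**Step 1: reproduce the stated sensitivities.** Solve the noncentral t for 80% power, two-sided 0.05. The noncentrality is d√n for the paired test and d√(n₁n₂/(n₁+n₂)) for the two-sample test.

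- Paired, in person: n = 31, 32, 33 give 0.520, 0.511, 0.503. Only 32 rounds to 0.51, so the in-person groups are 32 and 72 − 32 = 40.
- Paired, all: n = 43, 44, 45, 46 give 0.437, 0.432, 0.427, 0.422. Only 44 and 45 round to 0.43, so the full groups are 44/47 or 45/46.
- Two-sample check: 45/46 and 44/47 both give 0.594 (stated 0.59); 32/40 gives 0.674 (stated 0.67).

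**Step 2: online split by subtraction.**

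- Same group smaller in both sets: 44 − 32 = 12 and 47 − 40 = 7, or 45 − 32 = 13 and 46 − 40 = 6.
- Different group smaller: 46 − 32 = 14 and 45 − 40 = 5, or 47 − 32 = 15 and 44 − 40 = 4.
- A 9/10 online split would leave 34 to 36 in the smaller in-person group and a paired d of 0.480 to 0.495, not 0.51.

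**Step 3: effect on one per-visit between-group test.** Shift = D × (difference in online share). The unadjusted SD is the square root of the pooled value of 1 + p(1 − p)D², where p is the online share in each group. The adjusted test uses the sum of n₁n₂/(n₁+n₂) over the two modes.

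Worked case, 13/6 split and D = 0.5:

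- Shift: 13/45 − 6/46 = 0.158, times 0.5 = 0.079 SD. Unadjusted SD 1.020; 45 × 46/91 = 22.75.
- No true effect: noncentrality 0.079/1.020 × √22.75 = 0.37, so two-sided error is 6.6%.
- Effect 0.59, shift opposing: (0.59 − 0.079)/1.020 × √22.75 = 2.39, so power is 66%. With the shift favouring, power is 87%.
- Adjusted: 32 × 40/72 + 13 × 6/19 = 17.778 + 4.105 = 21.883; 0.59 × √21.883 = 2.76, so power is 78% whatever D is.

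All four splits (paired entries are D = 0.25 / D = 0.5):

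| Online split | Online share | Shift, SD | Error, % | Power opposed, % | Power favoured, % | Adjusted power, % |
|---|---|---|---|---|---|---|
| 12/7 | 27% v 15% | 0.03 / 0.06 | 5.2 / 5.9 | 74.6 / 68.5 | 83.0 / 85.4 | 78.5 |
| 13/6 | 29% v 13% | 0.04 / 0.08 | 5.4 / 6.6 | 73.4 / 65.7 | 84.0 / 87.2 | 77.9 |
| 14/5 | 30% v 11% | 0.05 / 0.10 | 5.6 / 7.3 | 72.0 / 62.7 | 85.0 / 88.8 | 77.1 |
| 15/4 | 32% v 9% | 0.06 / 0.11 | 5.8 / 8.2 | 70.6 / 59.6 | 85.9 / 90.3 | 76.1 |

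If D = 0, unadjusted power is 79.5%, so adjustment costs 1.0 to 3.4 points.

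**Step 4: direction in the crossover.** Let s be a stable shift in the A minus B difference. At T3 group A has just had the probiotic, so the probiotic-minus-placebo contrast carries +s. At T4 group B has, so it carries −s. The average of the two contrasts carries (s − s)/2 = 0. In a paired within-person test a stable level difference drops out of each participant's change.

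**The case against.** A reader might infer that the probiotic effect as a whole is confounded with fear of COVID-19. The documents do not support that, for four reasons.

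- **The crossover limits the harm.** Step 4 shows that a stable difference cannot favour the probiotic at both T3 and T4, and that it vanishes from the paired test, which the plan also names. The tests at each time point would also show such a difference at baseline. This stands. It confines the point to the per-visit between-group tests.
- **Separate allocation is not certain.** The abstract speaks of random allocation to online subgroups and the Trial design section of removal from the original allocation. The latter also speaks only of transfer to online assessment, and an odd/even division of 91 gives 46/45, close to the inferred totals. Fresh 1:1 allocation of the 19 onto 32/40 would be expected to give 41.5/49.5. Reaching 44/47 or closer needs 12 to 15 of the 19 in the smaller group, with binomial probability about 18%. The 19 may simply have kept their arm. On either reading the imbalance may be chance. With random allocation the unadjusted test keeps its error rate over repeated allocations, so the rates above are conditional on the inferred split.
- **The split is inferred** from effect sizes rounded to two decimals, and the recruitment flowchart, which may state it, is not shown.
- **Large effects need a large D.** With the 13/6 split, an error of 10.7% and a 31-point power loss (78% to 47%) need D = 1.0, for which the documents give no basis.

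It can also be said that pooling is sound because these outcomes were collected in person from everyone. That disposes of a measurement-mode effect, but not of a difference between the people. Nor is the test left open for a later plan: the article names it.

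**Conclusion.** The point holds in a limited form, as a minor one. The per-visit unpaired t-test on all 91 ignores subgroups that the plan itself describes and uses for cognition, and the stated sensitivities imply that the online share differs between groups by 12 to 23 percentage points. For D between 0.25 and 0.5 SD, the resulting shift is small against the detectable effect of 0.59. The loss of power when it opposes the effect is about 5 points at the mildest combination (79.5% to 74.6%) and about 20 at the strongest (79.5% to 59.6%).

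This rests on the inferred split, on an assumed D, and on D being stable over visits. The anxiety and mood scales are the most exposed. The documents support neither a claim that the trial's overall probiotic conclusion is biased nor a claim that allocation went wrong.

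**What to change.** For between-group comparisons on all 91 participants, replace the unpaired t-test with a linear model containing sequence group and an in-person/online indicator. Report the number of participants per group within each mode, which would also settle the inferred split, and state whether the 19 kept their original group or were allocated afresh.

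Cost: one covariate, a sentence or two in the plan and no new data. The downside is one degree of freedom and about 1 to 3 points of power if online and in-person participants do not differ; the detectable effect rises from 0.594 to about 0.60 to 0.62.

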Each participant was evaluated during four visits at the University Hospital Kralovske Vinohrady, Prague, or the National Institute of Mental Health, Klecany, Czech Republic. A subset of the participants agreed with the last follow-up visit (*n* = 16 in group A, *n* = 18 in group B). They continued the study for a further 3 months without any intervention after the study termination to see the long-term effect of microbiome changes. Therefore, they had the fifth visit in addition. The first, third, fourth, and fifth visits were planned at 3-month intervals with a tolerance of ±1 week. The second visit was added 1 week after the first one to let participants take test tubes and bring back baseline stool and urine samples.

All measures were included at each visit except the first two. For logistical reasons, all procedures were divided into two visits at the beginning of the trial. Participants were administered a cognitive battery, completed self-report measures, and received test tubes to collect stool and urine samples during the first visit. The second visit included a physical fitness evaluation and sample collection. Participants also received either probiotic or placebo tablets and fiber or placebo fiber tablets for the next 3 months. A detailed description of each visit is described in Supplementary material 1.

Whenever possible, the administration of cognitive tests was conducted by the same administrator for individual participants throughout the whole period of the study until the fourth visit. Only two administrators performed cognitive testing on the fifth visit to each institution.

The participants received 3,000 Czech crowns for their participation at the end of the study (i.e., the fourth visit), which is equal to 123 EUR or 140 USD at the current currency exchange.

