**FIGURE 4 F4:**
[figure not shown]
Expected hypotheses of cross-sectional (inter-group) and longitudinal (intra-group) comparisons at different time points. We expect improvement following the 3-month administration of probiotics (Δ: H1a, H2b, H2, H3). We expect no favorable change following the 3-month administration of placebo (H1b: =, H2a: =/<). Finally, we expect group B ending with the probiotic arm will have better outcomes than group A ending with placebo arm at time point T5 because of different intervals from the probiotic use (6 months for group A and 3 months for group B).

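### The between-group test is fixed as an unadjusted t-test at each visit, which gives up the precision available from each outcome's own pre-treatment value

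*Protocol article*

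**What the plan says.** Proposed analysis fixes the group comparison: "The analysis will proceed using a between-subjects unpaired *t*-test at each time point". The alternative it offers is to proceed "or using a within-subjects paired *t*-test to compare results between time points". The only further variable named is ApoE: "Additionally, we will include apolipoprotein E allele status and its influence on outcomes". Its role in the model is not stated.

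Power calculation gives the between-group detectable effects, d = 0.59 for all participants and 0.67 in person, for a "two-sample two-tailed *t*-test, assuming power = 0.8 and α = 0.05". The Figure 4 caption, under Anticipated results and hypotheses, describes "Expected hypotheses of cross-sectional (inter-group) and longitudinal (intra-group) comparisons at different time points".

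Trial design shows that a pre-treatment value exists for each type of outcome. For cognition and questionnaires: "Participants were administered a cognitive battery, completed self-report measures, and received test tubes to collect stool and urine samples during the first visit". For fitness and samples: "The second visit included a physical fitness evaluation and sample collection", at the visit where the first tablets were handed out. The same section reports that a few people were exchanged between the groups after a check for differences: "This ensured that both subgroups matched in age, education, gender, and ALBAV scores before the start of the trial".

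**The concern.** The article names the test, powers it and frames the inter-group hypotheses around it as cross-sectional. This is therefore a stated choice of method and not detail held over for an analysis plan. That the test uses each visit's score alone is inferred from the wording on time points and from the word cross-sectional; no covariate is mentioned anywhere for it.

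Three things are at stake.

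- **Precision.** The sample is fixed at 91, with 72 for in-person cognition. Variance that a person's own earlier score could explain stays in the error term.
- **Chance imbalance.** Matching covered four variables but not the outcomes. A baseline difference in, say, RAVLT, GDS or NfL carries straight into the T3 comparison.
- **Standard error.** If the groups were made alike on prognostic variables, the group difference varies less than the unadjusted t-test assumes, so its standard error is too large.

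The paired t-test does not fill the gap. It uses earlier scores, but only within a group, so it does not compare probiotic with placebo.

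**Working it through.** **Inputs.** From the article: N = 91 in total and 72 in person, two-sided α = 0.05, power 0.80, d = 0.59 and 0.67. Arm sizes are not in the readable text, so near-equal splits are assumed (45/46 or 44/47 in total; 36/36 to 32/40 in person). The baseline to follow-up correlation ρ and the share R² of outcome variance explained by the matched variables are not given. Both are assumptions, shown as ranges.

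**Step 1: reproduce the stated figures.** Noncentral-t power for two samples, solved for d at 80% power, gives 0.594 for 45/46 or 44/47 (stated 0.59) and 0.670 to 0.674 for 36/36 to 32/40 (stated 0.67). Both stated values are right for this test.

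**Step 2: adjust for the outcome's own baseline.** ANCOVA multiplies the residual variance by 1 − ρ², so detectable d is multiplied by √(1 − ρ²), starting from 0.594 (44/47) and 0.672 (33/39):

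| ρ | √(1 − ρ²) | All | In person | Power at stated d | Saving in N (ρ²) |
|---|---|---|---|---|---|
| 0 | 1.000 | 0.59 | 0.67 | 0.79–0.80 | 0% |
| 0.3 | 0.954 | 0.57 | 0.64 | 0.83 | 9% |
| 0.5 | 0.866 | 0.51 | 0.58 | 0.90 | 25% |
| 0.7 | 0.714 | 0.42 | 0.48 | 0.97 | 49% |
| 0.8 | 0.600 | 0.36 | 0.40 | >0.99 | 64% |

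For example, 0.594 × 0.866 = 0.514 and 0.672 × 0.714 = 0.480. Exact noncentral-t solutions agree to within about 0.001. Using five covariates instead of one for the degrees of freedom also moves detectable d by less than 0.001.

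**Step 3: effect of forced balance on the t-test.** Let Zx be the standardised group difference on a composite of the matched variables, kept only when |Zx| < c, and let Z be an independent standard normal. The true type I error of a nominal 5% test is approximately

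P( |√R²·Zx + √(1 − R²)·Z| > 1.96, given |Zx| < c ).

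- *Loose balance*, meaning only no significant difference (p > 0.05, c = 1.96): 4.4% at R² = 0.2 and 3.8% at R² = 0.4. Simulation with 36 per arm gives 4.5% and 3.8%.
- *Close balance* (p > 0.5, c = 0.674): 3.1% and 1.6%. Simulation gives 3.1% and 1.6%.
- *Exact balance*: 2·P(Z > 1.96/√(1 − R²)) = 2.8% and 1.1%.

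Shorter simulations of the first two settings gave 4.6% to 3.7% and 3.0% to 1.6%; the differences are simulation error. With no forced balance the t-test holds its 5% level. At R² = 0.25 under close balance, the true SD of the difference is 0.209 against a t-test standard error of 0.235. In the simulations with R² of 0.10, 0.25 and 0.49 under close balance, ANCOVA rejected in 4.8% to 5.2% of null runs.

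**The case against.** The strongest reply is that the unpaired t-test is valid, that its power figures are right, that the article calls its approach explorative, and that covariate lists usually belong in an analysis plan. The first two points stand in full. The last carries less weight here, because the article did not leave the method open.

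Several stronger readings are tempting, and the documents do not support them.

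- **A reader might infer that the standard errors are simply wrong, or that false positives rise.** Without forced balance the test is correct; with it, the error is conservative. The degree of balance is also unknown. Trial design mentions a check for significant differences and a few exchanges, yet says the groups matched. It then reports that 19 people were moved to online subgroups and describes no re-matching. The Abstract says the groups are matched at baseline, but whether this held among the 72 in person cannot be established.
- **A reader might infer that the plan ignores baseline altogether.** It does so only in the between-group test.
- **A reader might take baseline adjustment to be the main precision gain on offer.** In a crossover it is not. Under equal correlations and no carryover, the within-person treatment contrast has 1/[2(1 + ρ)] of the ANCOVA variance: 33% at ρ = 0.5 and 29% at ρ = 0.7. The absence of washout may bias that contrast, which is a separate matter.

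The gain may also be modest. Restricting entry to ALBAV ≤ 20 and using different RAVLT versions at T1, T3 and T4 could lower ρ. At ρ = 0.3, power rises only from about 0.80 to 0.83.

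**Conclusion.** The point holds as one of efficiency and residual imbalance in a stated method. The article's d = 0.59 and 0.67 are accurate for the unadjusted test, but that test is a poor use of the data collected. The gain from adjustment is small if ρ is near 0.3 and substantial from 0.5 upward, where the same power would need at least 25% fewer participants.

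The standard-error issue is secondary. It makes the test conservative by an amount that depends on how closely the groups were balanced and on an R² that the article does not give. It does not invalidate the test, and a claim of inflated type I error would be wrong. All sizes here rest on assumed ρ, R² and arm sizes.

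**What to change.** For the between-group comparison at T3, and at later visits as secondary, replace the unpaired t-test with ANCOVA. Regress the outcome on group, the same outcome's pre-treatment value (T1 for cognition and self-report, T2 for samples and fitness), age, education, gender and ALBAV score. Add assessment mode only for outcomes pooled across in-person and online participants. It is constant in the in-person cognitive models, because cognition is analysed separately by mode.

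Keep 0.59 and 0.67 as the unadjusted reference and report detectable d alongside them over a range of assumed correlations that includes low values, as in the table above.

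The cost is some analysis wording and a few degrees of freedom. Chance imbalance in the covariates adds slightly to the standard error, least for variables on which the groups really were matched. All the covariates are already collected. Adjustment does not repair the allocation by exchange or the missing washout, which need separate treatment.

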##### Brief cognitive tests

Brief cognitive tests included the Clock Drawing Test (CDT), our newly developed the ALBA test, and a short cognitive battery (ABACO). The CDT was evaluated using our developed and validated scoring system called BaJa. It was weighted in favor of assessing clock hands and suppressing the contribution of the clock itself. It ranged from 0 to 5 points. The time of 23:20 was chosen as it is cognitively more difficult than 11:10 or 5:40, as proven in our report (Bartos et al., 2016). The CDT was used without modification in all testing sessions. The CDT was omitted in online testing.

The ALBA test is a newly developed three-minute examination of intentional and incidental short-term memory, which could differentiate patients with mild cognitive deficits from cognitively normal individuals. The innovative test paradigm was based on a recall combination of one short six-word sentence and six gestures. First, a participant was asked to remember a sentence. The following distraction included a demonstration of six gestures and their incidental and immediate recall. The final task was sentence recall (Bartos, 2019). Two alternate forms of the ALBA test are available with good comparable psychometric properties in the Czech Republic (Bartos and Diondet, 2020). Online ALBA was the same as the in-person one (Polanska and Bartos, 2022). A completed example of an ALBA form with detailed administration and evaluation instructions is shown in Supplementary Figure 1. The ALBA educational video is freely available at: https://www.youtube.com/watch?v=LyCuWc0-Gro.

Our in-house cognitive battery, ABACO, consists of five brief tests: (1) the Reading Encrypted Sentences subtest, (2) the sentence learning and recall, (3) verbal fluency test, (4) the PICture Naming and Immediate Recall (PICNIR), whose educational video is freely available at https://www.youtube.com/watch?v=cbJGtPG-nVA, and (5) the Five or Four-line test. Detailed information about them is in Supplementary material 3.

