##### A comprehensive battery of neuropsychological tests

The Rey Auditory Verbal Learning Test (RAVLT) is intended for verbal memory evaluation. The test includes immediate verbal memory (A1), learning performance as a sum of five trials (A1–A5), proactive interference (B1), retroactive interference (A5–A6), and loss after consolidation (A6–A7) (Bean, 2011). In the Czech Republic, there are three alternative versions of RAVLT to eliminate the practice effect due to retest (Preiss et al., 2012). In the current study, we used them in version order: one at T1, two at T3, three at T4, and one at T5 (Figure 2). Online RAVLT testing was the same as that done in person.

The Trail Making Test (TMT) included parts A and B. Part A was used to evaluate processing speed, attention, and visuospatial ability. Part B, in addition to the mentioned functions, also assessed mental flexibility as a part of executive functions (Oosterman et al., 2010; Preiss et al., 2012). As there was no alternate form of the TMT in the Czech Republic, we used the same form for each test. The TMT was replaced with phonemic verbal fluency tests starting with the letters NKP during the online testing.

The Digit Symbol subtest from the Wechsler Adult Intelligence Scale III (WAIS-III) assessed the processing speed (Kaufman and Lichtenberger, 2005; Preiss et al., 2012).

Category (animal) fluency tests in person and online and phonemic fluency tests with initial letters NKP during online testing were used to evaluate executive functioning, language, and semantic memory (Lezak et al., 2012). Each verbal test took 1 min.

Online testing also included the Digit Span subtest from WAIS-III, which measured short-term verbal and working memory capacity (Preiss et al., 2012).

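### Within-group paired t-tests are left open as treatment tests, although treatment coincides with visit, practice and form order within each sequence group; d = 0.43/0.51 is the sensitivity of that uncontrolled change

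*Protocol article*

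**What the plan says.** The Protocol article's Proposed analysis section names two inferential procedures: an unpaired t-test between groups at each time point, or "using a within-subjects paired *t*-test to compare results between time points". The two are joined by 'or', and neither is ranked first for the treatment question. The legend of Figure 4 lists both inter-group and intra-group hypotheses. It expects improvement after three months of probiotic and no favourable change after three months of placebo.

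On the instruments:
- Trail Making Test: "we used the same form for each test".
- Clock Drawing Test: "The CDT was used without modification in all testing sessions".
- RAVLT: three alternative versions exist to counter practice, and "we used them in version order: one at T1, two at T3, three at T4, and one at T5".

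The Power calculation section gives "d = 0.43 in the matched-pairs two-tailed *t*-test, assuming power = 0.8 and α = 0.05", and then "This will be d = 0.51 in those tests when only in-person data could be used". It adds that "the sensitivity of the matched-pairs *t*-test is computed for the smaller group". For between-group comparisons it gives 0.59 and 0.67. The Trial design section states that there is no washout.

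**The concern.** In a two-sequence crossover, everyone in group A takes probiotic between T2 and T3 and placebo between T3 and T4, and group B takes them in the opposite order. Inside one group, treatment and visit cannot be told apart. Anything that moves scores from one visit to the next goes into the paired difference together with any probiotic effect.

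For cognition the article itself describes such influences. Two tests are repeated on the same form, and RAVLT version difficulty moves with visit because every participant meets the versions in the same order. Selection on a low electronic memory score (ALBAV of 20 or less) may add regression to the mean on related memory tests. For the biochemical, self-report and fitness outcomes there are no test forms of this kind, and the confounder is mainly period or calendar time.

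The other group measures these influences, but a paired test does not use it. If that test is read as the intra-group hypotheses suggest, practice, form or period change can be credited to the probiotic. The smaller detectable effects in the plan (0.43 and 0.51, against 0.59 and 0.67) also belong to this uncontrolled test.

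**Working it through.** **Inputs.** Two-sided α = 0.05, power 0.80, and d = 0.43, 0.51, 0.59 and 0.67 (Power calculation). Total 91 participants, 72 of them tested in person (Participant recruitment and allocation). The flowchart is not shown, so the group sizes are inferred below. The sizes of the practice, form or period shift are assumptions.

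**1. Reproducing the stated figures** with the exact noncentral t distribution.

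Paired: noncentrality = d·√n, df = n − 1.
- n = 44 gives d = 0.432 and n = 45 gives 0.427; both round to 0.43.
- n = 32 gives 0.511, which rounds to 0.51; n = 33 gives 0.503.

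Two-sample: noncentrality = d·√(n₁n₂/(n₁+n₂)), df = n₁ + n₂ − 2.
- 44/47 and 45/46 both give 0.594, stated as 0.59.
- 32/40 gives 0.674, stated as 0.67.

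All four figures reproduce, with groups of about 44–45 and 46–47 overall and 32/40 in person. A paired test over all 91 or all 72 would give 0.297 or 0.335. So 0.43 and 0.51 are one-group figures, as the article says.

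**2. What the paired test estimates.** For group A, T1 to T3:

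mean change = probiotic effect + practice + form difference + period

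For group B over the same interval:

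mean change = placebo response + practice + form difference + period

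The nuisance terms cancel in A minus B. They do not cancel in either line alone.

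**3. Size of the distortion.** Set the probiotic effect to zero and let δ be the shared shift in SD of change. The rejection probability is that of a noncentral t with noncentrality δ·√n. For n = 32 and δ = 0.3, the noncentrality is 0.3 × √32 = 1.70 against a critical value of 2.04, and the test rejects 37.6% of the time.

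| Assumed shift δ (SD of change) | n = 32 | n = 40 |
|---|---|---|
| 0.1 | 9% | 10% |
| 0.2 | 20% | 24% |
| 0.3 | 38% | 46% |

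These are the group sizes for in-person cognition, which is where test forms and practice matter. The article does not say whether A or B is the smaller group, so both columns apply.

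**4. Sensitivity of a controlled contrast.** For the A versus B difference in first-period change, the two-sample formula of step 1 applies with the SD of change as the unit: 0.59 (44/47) and 0.67 (32/40), before any gain from baseline adjustment. The numbers match those already printed for between-group comparisons, but the unit differs. A comparison of scores at T3 is in SD of the score.

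**The case against.** The sentence that names the paired test also names an unpaired test. At T3 both groups have had the same visits, forms and practice, so that comparison is free of them. This stands: the trial has a control for these effects, and the criticism is only that 'or' gives the controlled test no priority and that a single-time-point test does not use baseline.

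A reader might infer that the trial will declare benefit when group A is significant and group B is not, or that a non-significant placebo change will be taken to confirm no change. The documents state no such rule. Figure 4's legend gives expectations, and the figure itself is not shown. Error rates for that two-group pattern would therefore be those of an assumed rule.

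A reader might also take 0.43 as a wrong or mislabelled number. It is not: it reproduces, is called matched-pairs, and is said to refer to the smaller group. Nor does it belong to the in-person cognitive analysis, for which 0.51 is given.

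It could be urged that a crossover contrast over both periods would be far more sensitive. Under the same inferred splits it would detect about 0.30 (all) or 0.34 (in person) SD of the within-person difference, but only without carry-over. There is no washout, and the abstract expects the effect to last a further three months.

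Finally, the RAVLT versions were used to counter practice, so only their fixed order is open to objection. The Discussion calls the approach explorative, and a fuller analysis plan may specify a model. These points lower the severity. They do not make the stated paired test a test of treatment.

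**Conclusion.** The point holds in this form: the plan leaves an uncontrolled within-group test open as a route to a treatment conclusion, and its intra-group hypotheses invite that reading. That the paired test cannot separate treatment from visit follows from the design and needs no assumption. The size does: under assumed shifts of 0.1 to 0.3 SD of change, the nominal 5% error becomes roughly 9% to 38% with 32 people or 10% to 46% with 40, with group sizes inferred from the stated d values. The arithmetic in the Power calculation section is correct. What needs correcting is the use of 0.43 and 0.51, which describe change over time in one group in SD of the difference, not a treatment effect. Should-fix, given the stated explorative approach.

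**What to change.** 1. In Proposed analysis, state that paired t-tests are descriptive only.
2. Make the treatment test the between-group difference in change from T1 to T3, adjusted for baseline. For measures whose baseline is taken at T2 (samples, fitness), use T2 to T3. Analyse in-person cognition on its own, as already planned.
3. If both periods are used, fit a mixed model with sequence, period and treatment and a random participant effect. Label it supportive, because there is no washout and persistence is expected.
4. Reword the intra-group hypotheses in Figure 4 as descriptions of expected course.
5. In Power calculation, label 0.43 and 0.51 as the sensitivity of a one-group change over time in SD of the difference. Quote about 0.59 (all) and 0.67 (in person) SD of change, before the gain from baseline adjustment, for the treatment contrast.

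Cost: wording and a standard model in R, with no new data. The price is that the more favourable paired figure no longer supports the treatment claim.
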